#### Serious adverse events/reactions

Serious adverse events (SAE) or reactions can be defined as any untoward medical occurrence or effect that at any dose

• results in death,

• is life-threatening,

• requires hospitalisation or prolongation of existing inpatients hospitalisation,

• results in persistent or significant disability or incapacity,

• is a congenital anomaly or birth defect.

#### Expected serious adverse events/clinical outcomes due to underlying acute coronary syndrome

• Myocardial Infarction (MI)

• Stroke

• Revascularisation

• Major Bleed

• Death

#### Drug related serious adverse reactions

• Serious Infections – Previous trials conducted by Amgen demonstrated an incidence of serious infections in 1.8% of IL-1ra treated patients compared to 0.7% in placebo group. There were no on-study deaths due to serious infectious episodes.

• Neutropenia – Administration of IL-1ra was associated with neutropenia (ANC < 1.5 × 10^9^/I) in 2.4% of patients compared with 0.4% of placebo patients. None of these patients had serious infections associated with the neutropenia.

#### Reporting of serious adverse events/reactions

The CRF will contain specific SAE reports relating to the SAEs/clinical outcomes listed above. The investigator will complete the SAE report in the CRF, including date of event, admissions, diagnosis details, date of discharge or death. Those SAEs considered a suspected unexpected serious adverse reaction (SUSAR) will be marked "possible SUSAR" on the SAE report. The investigator will also attach a discharge/medical summary and fax to the CTEU with the SAE report within 24 hours. Any other SAE not fitting the criteria above will be reported on the "other SAE" report in the CRF.

The CTEU will review all serious adverse event/reaction reports before sending an electronic copy to the SAEC for adjudication. All reported SAE/Rs will be adjudicated by the SAEC to assess the seriousness and causality between the IMP and/or concomitant therapy and serious adverse event/reaction. This assessment must take place within two working days upon receipt of the electronic copy of the form. If the SAEC judge the SAE/R to constitute a SUSAR, the CTEU will ensure expedited reporting procedures are followed.

#### Suspected unexpected serious adverse reactions (SUSARS)

A SAR can be considered unexpected when the adverse reaction, the nature or severity of which is not consistent with the applicable product information. All suspected unexpected serious adverse reactions related to an IMP, which occur during the trial, are subject to expedited reporting.

#### Reporting of SUSARs

The CTEU will unblind the SUSAR report before sending it electronically to the SAEC with the medical summary attached. The SAEC will review the report and summary within two working days and adjudicate whether the event constitutes a SUSAR. The SAEC will inform the CTEU of their decision to ensure expedited reporting procedures are followed if necessary.

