### Trial design

Randomised, double blind, placebo-controlled multi-centre phase II clinical trial

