### Study treatment

Eligible patients will be randomised in equal proportions between IL-1ra and placebo, receiving either a once daily, subcutaneous (s.c). injection of IL-1ra (dose 100 mg per 24 h) for 14 days, or a daily s.c. injection of placebo for 14 days. The hospital pharmacist will issue the relevant drug package. (Please see appendices for pharmacy information).

The study drug and placebo will be provided by Amgen Inc in its commercially available recombinant form which is in clinical use for the treatment of arthritic conditions. The study drug and placebo will be relabelled by Amgen, in collaboration with CTEU according to MHRA guidelines.

The first dose of IL-1ra will be given within 24 h +2 h of the positive Troponin. Injections will be given at a standardised time (24 ± 2 h after the previous dose), immediately after blood sampling. IL-1ra or placebo will administered to the patient by the research nurse while the patient is in hospital. During the hospital stay, the patient will be taught to self-administer the injection by the research nurse and on discharge will continue at home. This has proven possible in other ACS trials that required self injection of subcutaneous heparin [36]. Full written guidance on self injection will also be provided to patients. If self injection is found not to be possible in an individual patient for unexpected reasons, an alternative method will be sought (e.g. district nurse, or attending the hospital) to try and maintain full compliance with scheduled study drug regimen after discharge. Patients will also be asked to complete a daily injection diary. All personnel will be blinded to the identity of the syringe contents.

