#### Clinical event review committee

The Clinical Event Review Committee will review adverse events during the study and adjudicate them to ensure the events meet the definitions given. Each event will be independently adjudicated by two committee members. A third committee member will be called to adjudicate an event if agreement is not reached by two members. The adjudications will be blind to the knowledge of which arm of the trial the patients are in.

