#### Safety reporting

The University of Sheffield (Sponsor) has delegated responsibility for pharmacovigilance to the trial co-ordinating centre (Clinical Trials and Evaluation Unit (CTEU) of the Royal Brompton Hospital, London).

The CTEU will be responsible for recording all reported serious adverse events from investigational trial sites, reporting all serious adverse events to a constituted serious adverse events committee (SAEC) for review and expedited reporting of suspected unexpected serious adverse reactions (SUSARs) in accordance with statutory regulations. The SAEC will consist of one nominated investigator from each trial site who can provide clinical expertise to adjudicate serious adverse events and determine if they are SUSARs, and advise the CTEU whether expedited reporting is required.

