#### Unblinding

The treatment code must not be broken except in medical emergencies when the appropriate management of the patient necessitates knowledge of the treatment. Each pharmacy will keep a copy of the randomisation allocation list, in case unblinding is necessary. Should a SUSAR occur, the CTEU will unblind the patient and follow expedited reporting procedures.

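### Reports flagged as possible SUSARs are unblinded before the SAEC, made up of site investigators, has judged causality and SUSAR status; the order should be reversed

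*Protocol article*

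**What the plan says.** The Trial design section describes the study as "Randomised, double blind, placebo-controlled multi-centre phase II clinical trial". Four sections then govern serious events and the code break.

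- **Safety reporting** sets up the serious adverse events committee: "The SAEC will consist of one nominated investigator from each trial site". These members determine which events are SUSARs and advise the CTEU whether expedited reporting is needed.
- **Reporting of serious adverse events/reactions** has the site investigator flag a suspected case as a possible SUSAR and fax it to the CTEU. On the committee's task it says: "All reported SAE/Rs will be adjudicated by the SAEC to assess the seriousness and causality between the IMP and/or concomitant therapy". It mentions no unblinding.
- **Reporting of SUSARs** then says: "The CTEU will unblind the SUSAR report before sending it electronically to the SAEC with the medical summary attached". The committee has two working days to decide whether the event is a SUSAR, and expedited reporting follows if needed.
- **Unblinding** says: "The treatment code must not be broken except in medical emergencies when the appropriate management of the patient necessitates knowledge of the treatment". It adds one further case: the CTEU unblinds the patient if a SUSAR occurs.

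Separately, **Expedited reporting of SUSARs** has the CTEU unblind SUSAR reports before they go to the MHRA and REC.

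**The concern.** Causality is a judgement, and knowledge of the arm can sway it. Once an event is known to have occurred on placebo it can hardly be attributed to the study drug; once it is known to have occurred on active treatment, attribution comes more easily. A committee that sees the allocation first risks making attribution depend partly on allocation. That matters here because the drug is being tested in a new indication.

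The second cost is to the blind. The people who receive the allocation are investigators in the same trial. Where the committee decides that the event is not a SUSAR, the code has been broken and disclosed with no regulatory need, and it cannot be restored.

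**Working it through.** No arithmetic applies. The check is of the order of steps and of whether the sections agree.

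**Order of steps as written**

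1. The site investigator flags the event as a possible SUSAR (Reporting of serious adverse events/reactions).
2. The CTEU breaks the code on that report (Reporting of SUSARs).
3. The unblinded report goes to the SAEC, one nominated investigator per site (Reporting of SUSARs; Safety reporting).
4. The SAEC judges seriousness and causality and decides whether the event is a SUSAR (Reporting of serious adverse events/reactions; Reporting of SUSARs).
5. If it is, the CTEU sends an unblinded report to the MHRA and REC (Expedited reporting of SUSARs).

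Step 2 comes before step 4, so allocation is known to the adjudicators when they decide. Expedited reporting after step 4 is conditional, so the protocol itself foresees flagged reports that turn out not to be SUSARs. Those have been unblinded all the same.

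**Does the Unblinding section permit step 2?** It allows a code break in a medical emergency, or by the CTEU when a SUSAR has occurred. At step 2 the protocol's own decision on SUSAR status has not been made. Nor does the section provide for passing the allocation to site investigators.

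**Is step 2 needed for regulatory reporting?** No. Step 5 already contains the unblinding that the regulators require, done by the CTEU.

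**Is the committee's practice uniform?** No. For other serious events, the protocol has the same committee judge causality and mentions no code break. Only flagged reports arrive unblinded, so one committee works to two standards.

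**Which outcomes are touched?** The primary outcome is a laboratory measure, the AUC of hsCRP over seven days. None of the listed secondary outcomes is assigned to the SAEC for adjudication.

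**The case against.** Several points on the other side are fair.

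- **There is a blinded first judgement.** The site investigator considers the event a suspected SUSAR and flags it before any code break. That stands, but it is the trigger for review. The decision on causality and expedited reporting belongs to the SAEC.
- **The Unblinding section has a SUSAR exception.** It does, and since a SUSAR is by name only suspected, a flagged report could be read as falling under it. But the protocol separates the flag from the SAEC's finding, and the exception covers unblinding by the CTEU, not disclosure to investigators. What remains is a conflict of timing and recipient.
- **Few patients are affected.** This also stands: only flagged reports are unblinded, and one nominated investigator per site sees them, not all site staff.

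Some stronger readings are tempting but not supported.

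- A reader might see a contradiction with the statement "The adjudications will be blind to the knowledge of which arm of the trial the patients are in". That sentence governs the Clinical Event Review Committee, a different body. It is a useful contrast, and it limits the concern, because that committee's adjudication stays blind.
- A reader might cite "All personnel will be blinded to the identity of the syringe contents" as a breached rule. It stands in the section on giving the injections and is not a rule on safety reporting.
- A reader might size the problem from the serious infection rates of 1.8% and 0.7%: with 186/2 = 93 per arm, 93 × 0.018 + 93 × 0.007 = 1.674 + 0.651 ≈ 2.3 events. That is not a count of SUSARs. The protocol already lists serious infection as a drug-related serious reaction, whereas a SUSAR must be inconsistent with the product information. The rates also come from previous manufacturer trials whose population and treatment duration are not given in that section.
- A reader might infer that a planned comparison between arms is biased. The protocol lists no outcome that the SAEC adjudicates, and gives nothing from which the size of any bias could be found.

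**Conclusion.** The point holds in a limited form. The sequence under Reporting of SUSARs discloses allocation to trial investigators before they adjudicate, including for events that they then reject as SUSARs. It goes beyond what the Unblinding section allows and sits badly with a double-blind design.

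Its size cannot be computed: the protocol gives no expected number of flagged reports, and the number is probably small. Each such report exposes one patient's allocation to the SAEC's members, which is three people if each of the three centres nominates one. The consequence is a risk of bias in safety attribution and a partial loss of the blind among those members. No direct effect on the hsCRP comparison or on the blinded event committee is shown.

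The conclusion assumes that the sections mean what they say, and that no other document restricts what the SAEC sees or gives it independent members. The article states neither safeguard.

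**What to change.** Reorder the steps under Reporting of SUSARs:

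1. The CTEU sends the SAEC a blinded report with the medical summary.
2. The SAEC judges seriousness, causality and expectedness without knowing the arm. Expectedness can be judged against the product information on the assumption that active drug was given.
3. The CTEU breaks the code only for events judged to be SUSARs, and then submits to the MHRA and REC, as Expedited reporting of SUSARs already provides.

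Align the wording of Reporting of SUSARs, Expedited reporting of SUSARs and Unblinding, so that all three place the code break after the SAEC's decision and name who receives the allocation.

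The cost is a text change. The two-working-day review stays, and the 7-day and 15-day limits still run from the time the CTEU becomes aware of the event. Further safeguards, such as barring the reporting site's member from voting or using an unblinder outside trial management, would be new rules rather than reordering. They are optional, and the fix does not depend on them.

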#### Expedited reporting of SUSARs

All SUSARs will be reported to the MHRA and NHS REC, by the trial co-ordinating site (CTEU). All SUSAR reports will be unblinded by the CTEU prior to submission. A SUSAR, which is fatal, or life threatening will be reported to the MHRA and the main REC by the CTEU as soon as possible and within 7 days after the CTEU become aware of the event. A SUSAR, which is not fatal, or life threatening must be reported to the MHRA and main Research Ethics Committee (REC) as soon as possible and within15 days after the CTEU become aware of the event. The CTEU will inform all trial investigators of all reported SUSARs within 15 working days.

#### Annual reporting

The CTEU will submit annual safety reports of all suspected serious adverse reactions in accordance with regulatory requirements to the MHRA and Main REC. Annual safety reports will be submitted to the MHRA on the date of the original clinical trials authorisation. Annual progress reports will also be submitted to the main REC on the same date. Annual safety reports will also be submitted to the Data Monitoring Committee for review.

#### Participant withdrawal

Investigators must ascertain the reasons for the withdrawal due to adverse events, failure to attend, non-compliance, withdrawal of consent or other reasons. The withdrawal form must be faxed to the CTEU within five working days, unless withdrawal is due to a SAE, in which case the investigator will follow SAE reporting procedures.

#### Unblinding

The treatment code must not be broken except in medical emergencies when the appropriate management of the patient necessitates knowledge of the treatment. Each pharmacy will keep a copy of the randomisation allocation list, in case unblinding is necessary. Should a SUSAR occur, the CTEU will unblind the patient and follow expedited reporting procedures.

#### Indemnity

Patients that are enrolled into the study are covered by indemnity for negligent harm through the standard NHS Indemnity arrangements. The University of Sheffield has insurance to cover for non-negligent harm associated with the protocol. IL1-ra is commercially available for the treatment of inflammatory arthritic conditions. The rate of serious side effects attributable to treatment is <1%. This will include cover for additional health care, compensation or damages whether awarded voluntarily by the Sponsor, or by claims pursued through the courts. Incidences judged to arise from negligence (including those due to major protocol violations) will not be covered by study insurance policies. The liability of the manufacturer of IL1RA (Amgen Corporation) is strictly limited to those claims arising from faulty manufacturing of the commercial product and not to any aspects of the conduct of the study.

#### Ethics

This study will conform with the Declaration of Helsinki guidelines on research involving human subjects. The study protocol will be submitted to the Multi-centre Research Ethics Review Committee, and Ethics Committees at each centre participating in the study and approval obtained before the study commences.

#### Publication policy and dissemination of results

The results from the trial will be submitted for publication in a major journal irrespective of the outcome. The Trial Steering Committee will be responsible for approval of all manuscripts arising from the study prior to submission for publication. Sub-studies of centre-specific data may only be carried out with the knowledge and approval of the Trial Steering Committee.

Any individual authorship of presentations and reports related to the study will be on behalf of the collaborative group. The final follow-up study results paper will name local co-ordinators as well as those involved in central co-ordination and trial management.

At the end of the study, patients will be able to request a copy of the results of the study from the investigator at that site.

#### Proposed study timetable

March 2006 – Grant awarded by MRC

Jan 2007 – Recruitment starts

Dec 2009 – Recruitment completed

Jan 2010 – Last patient completes 30 day follow up

2010 – Publication of data

## Abbreviations

CRP – C Reactive Protein. IL-1 – Interleukin 1. IL-1ra – Interleukin 1 receptor antagonist. ACS – Acute Coronary Syndrome. ECG – Electrocardiogram. AUC – Area under the curve. REC – Research Ethics Committee. IMP – Investigational Medicinal Product.

#### Labelling

Examples of the labelling can be found appended to the Summary of Product Characteristics.

#### Storage

Store in a refrigerator (2°C – 8°C).

#### Manufacturer's authorisation

EU/1/02/203/001-003

#### Transportation of samples to core lab

Samples will be stored in -20°C freezers at each centre. All participating centres have research freezers available for use. FedEx will then send samples in batches to the core labs.

## Appendix 2 – Sub study protocols

### 1. Cardiac Magnetic Resonance imaging sub study

The Leeds cohort of patients will undergo baseline and follow-up Gadolinium enhanced CMR as a quantitative measurement of extent of myocardial injury. We wish to evaluate the possible mechanisms of any potential benefit and, therefore, feel that investigation of myocardial function, infarct size and oedema is justified. CMR is an accurate and reproducible technique for making these assessments. CMR can distinguish between scar tissue (following myocardial infarction/acute coronary syndromes) and normal (viable) myocardium using the late gadolinium hyper-enhancement technique [38,39]. CMR can also differentiate acute from chronic infarction, based on the principle that acute infarctions are surrounded by tissue oedema secondary to the inflammatory process [40]. Thus, CMR is well suited to extend our understanding of the mechanism of any potential benefit from IL-1ra treatment at the time of NSTEMI ACS. Therefore, we plan a CMR sub-study in the Leeds patients who will have a CMR scan within 48 h of presentation using the protocol outlined below. A follow-up scan, using the same protocol, will be performed after the completion of randomised therapy. Quantification of myocardial oedema, myocardial scar and ventricular volumes/function will be performed on both scans. Exploratory statistical analysis will be undertaken for serial change in these measures within patients and between groups.

#### CMR imaging procedure

1) Localisers and breath-hold plan scans to define LV short axis. 2) Resting wall-motion sequence. Multiphase HLA, VLA and short axis cine stack (10–12 slices) using a fast gradient echo sequence to assess wall motion. Then in identical scan planes; Breath hold, black blood, T2-weighted triple inversion recovery sequence. 3) Late gadolinium hyper-enhancement CMR: T1-weighted, segmented inversion-recovery sequence 15 minutes after intravenous injection of Gadolinium (0.2 mmol/kg). This protocol will be piloted on 20 patients before the start of the main clinical trial.

### 2. ST-Holter segment analysis sub study

As soon as possible after recruitment, between days 2 and 4 of treatment, Sheffield patients will be identified as suitable for ST segment monitoring. Exclusion criteria will include bundle branch block, significant conduction abnormality, digoxin therapy or serious electrolyte disturbance. The presence of other potentially confounding features, such as mitral valve prolapse, posture change, changes due to body habitus and temperature change will be assumed to be similar in the two groups. A Holter monitor will be attached using the 3 standard leads for 24 h. If catheterisation be performed during the period of the recording, an appropriate entry will be made on the time log prior to the monitor being removed and replaced afterwards. If revascularisation be undertaken, the monitor will not be replaced. The monitor will be removed by one of the ECG technicians after 24 h (or as just stated) and analysed by [name] (an experienced ECG technician who works in Sheffield), using the standard Reynolds protocol for ST segment analysis. She will be blinded to the identity of the treatment. The number of ischemic events, their frequency and total duration will be compared in both treatment groups.

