### Concomitant treatments and procedures

All patients will receive standardised additional treatments according to best practice including aspirin, clopidogrel, heparin (intravenous or low-molecular weight), a glycoprotein IIb/IIIa inhibitor and a statin. Other medication will be at the physicians' discretion. It is the intention that all patients will proceed to coronary angiography according to current guidelines, and subsequent revascularisation if necessary.

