#### Secondary outcome measures (comparison between treatment and control of)

1. Mean hsCRP at 7, 14 and 30 days

2. Area under the curve of Troponin-I

3. vWF and IL-6

4. ST segment depression on Holter monitor

5. Myocardial injury as determined by Gadolinium enhanced CMR scan

6. Forearm endothelial cell response

7. Incidence of major adverse cardiovascular events (MACE) at 30-days, three months and at one year.

8. Flagging with Office of National Statistics (ONS) for up to 5 years.

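### Holter event number and total ischaemic duration are compared between arms without relating them to monitored time, although recording ends at revascularisation

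*Protocol article*

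**What the plan says.** The Secondary outcome measures list includes "ST segment depression on Holter monitor". The detail is in Appendix 2, section 2 (ST-Holter segment analysis sub study), which applies to Sheffield patients only.

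- **Planned length:** "A Holter monitor will be attached using the 3 standard leads for 24 h".
- **Window:** "As soon as possible after recruitment, between days 2 and 4 of treatment, Sheffield patients will be identified as suitable for ST segment monitoring".
- **Catheterisation during the recording:** "an appropriate entry will be made on the time log prior to the monitor being removed and replaced afterwards".
- **Revascularisation:** "If revascularisation be undertaken, the monitor will not be replaced".
- **Comparison:** "The number of ischemic events, their frequency and total duration will be compared in both treatment groups".

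Under Concomitant treatments and procedures the protocol adds: "It is the intention that all patients will proceed to coronary angiography according to current guidelines, and subsequent revascularisation if necessary". It gives no expected revascularisation rate and no timing relative to the recording.

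**The concern.** The protocol fixes both the rule that ends a recording and the quantities to be compared, and two of the three quantities do not fit the rule. A count of ischaemic events and a total ischaemic duration both rise with hours watched. A patient monitored for 12 h has about half the opportunity to record events of one monitored for 24 h.

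Recording ends at an event that happens after randomisation and is plausibly driven by the ischaemia being measured. If the drug reduces ischaemia and so the need for revascularisation, treated patients are watched for longer and accumulate more counted events per patient. That works against showing the benefit. With one centre contributing, there is little precision to spare.

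**Working it through.** The protocol gives no sample size, event rate, revascularisation rate or power for this sub-study, so there is no stated figure to reproduce. What follows is illustrative.

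**1. Monitored time.** Inputs: planned recording of 24 h (Appendix 2); share *p* of recordings ended by revascularisation (assumed); mean time to that end of 12 h, as for cut-offs spread uniformly over 24 h (assumed).

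Mean monitored hours = 24(1 − *p*) + 12*p*.

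| *p* | Calculation | Mean hours |
|---|---|---|
| 10% | 21.6 + 1.2 | 22.8 |
| 20% | 19.2 + 2.4 | 21.6 |
| 25% | 18.0 + 3.0 | 21.0 |
| 30% | 16.8 + 3.6 | 20.4 |
| 40% | 14.4 + 4.8 | 19.2 |
| 50% | 12.0 + 6.0 | 18.0 |

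If the underlying ischaemia rate is the same in both arms, the expected ratio of raw counts (or durations), IL-1ra to placebo, equals the ratio of hours:

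- 20% v 40% cut short: 21.6/19.2 = 1.125
- 10% v 40%: 22.8/19.2 = 1.19
- 25% v 50%: 21.0/18.0 = 1.17
- 20% v 30%: 21.6/20.4 = 1.06
- 30% in both arms: ratio 1.00, but 1 − 20.4/24 = 15% of observation time is lost

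**2. Simulation.** Inputs: 31 patients per arm (about 62 per centre from Screening and enrolment, split 1:1 as in Study treatment, before exclusions); gamma-Poisson events with mean 2 per 24 h (assumed); cut-off uniform over 24 h; Mann-Whitney test at 5%; 3000 runs per scenario. Near 5% the simulation standard error is √(0.05 × 0.95/3000) = 0.4 percentage points. The per-hour ratio is total events over total hours.

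| Truncation, placebo v IL-1ra | True rate ratio | Raw-count ratio | Per-hour ratio | Rejection rate, raw | Rejection rate, per hour |
|---|---|---|---|---|---|
| 30% v 30%, unrelated to ischaemia | 1 | 1.00 | 1.00 | 4.9% | 4.9% |
| 30% v 20%, unrelated | 1 | 1.06 | 1.01 | 4.6% | 4.6% |
| 50% v 25%, unrelated | 1 | 1.17 | 1.00 | 7.6% | 5.5% |
| nominal 30%, driven by ischaemia | 1 | 0.99 | 1.00 | 4.7% | 4.7% |
| 30% v 30%, unrelated | 0.67 | 0.67 | 0.67 | 16.7% | 16.7% |
| nominal 30%, driven by ischaemia | 0.67 | 0.74 | 0.71 | 12.4% | 14.2% |
| nominal 50%, driven by ischaemia | 0.67 | 0.74 | 0.69 | 10.1% | 12.8% |

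In the ischaemia-driven rows a patient's chance of truncation rises with that patient's own event rate, by the same rule in both arms. When the drug lowers the rate, it therefore also lowers truncation. In the nominal 30% case, monitored time becomes 20.6 h on placebo and 21.6 h on IL-1ra.

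**3. How much a per-hour measure recovers.** The raw count misses the true ratio by 0.744 − 0.67 = 0.074. The per-hour ratio misses by 0.708 − 0.67 = 0.038 (nominal 30%) or 0.694 − 0.67 = 0.024 (nominal 50%). It removes about half to two-thirds of the distortion. The rest remains because patients with the most ischaemia contribute the fewest hours, and more of them are on placebo.

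**The case against.** **Randomisation protects the comparison.** Allocation is 1:1 and double blind, and the Holter reader is blinded. Monitored time is therefore equal in expectation unless treatment itself changes revascularisation. A chance imbalance is noise that the test already allows for. This stands. A reader might infer that unequal monitored time will show up as a false treatment effect, and the protocol does not support that. With no drug effect, rejection stayed at 4.6% to 4.9% in three of four scenarios and rose to 7.6% only under an assumed 50% v 25% split. A spurious effect would also need revascularisation to fall without any fall in ischaemia, and it would then look like harm from IL-1ra.

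**Short recordings may be few.** A reader might also infer that truncation will be common because angiography is intended for everyone. The protocol does not say so. Revascularisation is only as needed, its timing is not given, and it must fall inside one 24 h recording on days 2 to 4 to matter. This stands too.

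**The plan may already handle it.** Frequency is listed separately from number and may well mean a rate, and a time-log entry is required when the monitor is removed for catheterisation. Both points help, but frequency is undefined and the other two comparisons still ignore monitored time.

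**This is detail for the analysis plan.** The model and the handling of incomplete recordings can be left there. But the protocol itself names the quantities to compare alongside a stopping rule that two of them do not fit. That is a stated choice, not missing detail.

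**Conclusion.** The point holds in a limited form. Number of events and total duration are not tied to monitored time in a design that ends recording at an outcome-related event after randomisation. The distortion arises only if IL-1ra changes whether or when patients are revascularised. Its most plausible form is dilution of a real benefit: in the simulated cases a 33% reduction appears as about 26%. Balanced truncation unrelated to ischaemia costs information, not validity.

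The ratios of 1.06 to 1.19 rest on assumed truncation splits, a mean cut-off of 12 h and identical ischaemia in both arms. The 0.74 rests on an assumed event rate and an assumed link between ischaemia and revascularisation. None of these comes from the protocol.

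Importance is low to moderate. This is a single-centre sub-study of a secondary outcome, and the primary CRP analysis and the sample size are unaffected. The change is worth making because it costs so little.

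**What to change.** In Appendix 2, section 2:

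1. Define frequency as ischaemic events per monitored hour. Make this, with ischaemic minutes as a percentage of monitored time, the between-arm comparison. The choice of model can be left to the analysis plan, provided it accounts for each patient's monitored hours.
2. Keep raw number and total duration as descriptive summaries only.
3. State that both removal and replacement times are logged, including removal at revascularisation. The present text expressly requires an entry only before removal for catheterisation.
4. Report monitored hours and the reason for ending the recording, by arm.
5. Add a sensitivity analysis for truncation related to ischaemia, because the per-hour measure removes only part of that distortion. One option is to assign the unobserved hours a range of multiples of the rate seen before removal. Another is to repeat the comparison over an early stretch that most patients complete.

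The cost is some analysis wording, one more logged time and slightly more analysis work. Rates from very short recordings are imprecise, which is a reason to weight by hours. Neither patient care nor the rule for removing the monitor needs to change.
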